#### Impact measures of the PICU liberation program implementation

Orchestrated Testing will be used to assess implementation success, the impact of the PICU Liberation intervention, and identify essential components for best practise [32]. A clear implementation plan and structure for interaction are two of the Orchestrated Testing requirements. (generated in study phase 1, see Fig. 1 and Appendix 1). In our study, the number of bundle components in Phase 1 represents existing practise and Phase 4 represents bundle implementation, hence a Factorial (or Fractionated factorial) matrix is critical. In step 4, the results will be analysed. The ability to duplicate the study findings will be tested internally (repeat plan-do-act cycles) and externally, as part of a proposed secondary study testing bundle implementation at a separate PICU in Australia.

Control charts depicting the PICU Liberation metrics will be used to track exposure to the intervention/consistency. (as described in Table 3 and Fig. 4 below).

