### Strengths and weaknesses of this study

This will be the first comprehensive study to investigate the feasibility and impact of the A2F bundle adaptation to an Australian PICU.

The hybrid mixed methods study design will allow reporting of a detailed adaptation and implementation guideline, including clinical resources (and investment) required, to adopt the PICU Liberation bundle in other children’s hospitals.

The PICU Liberation intervention is not amendable to blinding of patients, family or clinicians or randomisation. The primary limitation is the single-centre design.

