## Methods

### Study protocol

This single centre prospective before-after hybrid trial-and-implementation quality improvement initiative will be conducted in a 36-bed mixed medical-surgical-cardiac PICU in a large children’s hospital in Brisbane (Australia) with approximately 2000 admissions per year. The adaptation, as well as the implementation process, will involve the children’s parents, carers, PICU clinicians and researchers.

Waiver of ethical approval and consent for this clinical innovation was obtained from the Children’s Health Queensland Ethics Committee as the intervention is a quality improvement project. This study will be performed in accordance with the ethical principles of the Declaration of Helsinki, ICH GCP for Guidance on Good Clinical Practice and NHMRC National Statement on Ethical Conduct in Research Involving Humans [23, 24].

Children will be identified by screening consecutive admissions to the PICU by the interdisciplinary research and quality improvement team, including PICU medical, nursing and allied health staff. Their data will be analysed if inclusion criteria are fulfilled and no exclusion criteria present. (Table 1).

**Table 1 Tab1:** Inclusion and exclusion criteria

Inclusion criteria	Admission to study PICU
	≤18 years of age on admission
	PICU LOS ≥ 24 h
	Expected survival ≥1 year post PICU admission
Exclusion criteria	Paediatric Advanced Resuscitation Plan (PARP) actively enacted during admission
	​Severe chronic disability precluding PICU liberation program participation
	Minimally consciousness state on admission

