Activities:Implement PICU Liberation “check-ins” - a nurse-led, interdisciplinary rounding checklist - to ensure communication and application of all relevant bundle elements as clinically appropriate. The Plan-Do-Study-Act cycle will be utilised in the delivery of each bundle element, and adaptation will occur based on clinician and family feedback, and feasibility assessment following the initial roll-out to improve usability.Develop and implement a daily goals checklist for use during daily multidisciplinary ward rounds, which will include specific reference and reminders for each relevant bundle element.Provide education and training for PICU staff regarding the Liberation program via various mediums (new staff orientation, online, workshops, nursing education program curricula (theory modules and workbooks), individual bundle element in-services, bedside teaching, videos, breakfast sessions, case studies, simulations). This education will introduce the individual components of the bundle, use of assessment items, and recommendations for clinical actions based on assessment results. While education will be consolidated early in the implementation phase, it will be purposively staggered over all phases to ensure adequate updates and inclusion of new PICU staff. Education will be offered to nursing, medical, and allied health staff. Outreach and education to other hospital departments and services including non-clinical areas will be provided to ensure adequate understanding on downstream effects of PICU Liberation.Develop awareness of the relevance and importance of PICU Liberation program and its role in reducing PICU-acquired complications and improving short- and long-term outcomes.Repeat audits of A2F Bundle compliance, patient outcomes and satisfaction by parents as well as staff satisfaction and wellbeing assessments.Assess a) perceptions from staff about the PICU Liberation program and the implementation process; b) perceived barriers and facilitators to its implementation; c) how PICU Liberation has affected care; d) staff knowledge of key bundle elements and components, and e) perception of staff about the PICU Liberation educational resources. Note that the structural aspects (i.e., relative socioeconomic resources, political norms, policies) and their influence will not form part of this assessment.Continue to dynamically assess barriers and enablers to inform the continuous adaption of the A2F bundle operationalisation to improve the feasibility and implementation success.Focus group interviews with key stakeholder groups (i.e., family members, clinicians and administrative leaders) will be conducted to determine a) perceptions of PICU Liberation and the implementation process; b) perceived barriers and enablers to its implementation; and c) how PICU Liberation has affected care. All interview approaches will be used to maximise involvement, including face-to-face interviews, teleconferenced focused groups, and semi-structured interviews using separate interview guides. Families may be interviewed following exposure to the intervention and patient care experience (i.e., at or after PICU discharge). Clinicians may be interviewed mid-implementation to understand their impressions of the knowledge application process and adapt the implementation procedures if necessary.

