#### Phase 4 - assessment of the feasibility of A2F bundle adaptation and the implement success of the PICU liberation program

##### Objectives

Assess feasibility, adherence, acceptability, and impact of pilot study roll-out including on PICU related complications.

Activities:Assess the feasibility of adapting the A2F bundles in PICU.Measure bundle fidelity (i.e. bundle compliance/adherence), using both quantitative analytic and qualitative methods (Table 2, Table 4). If a low degree of fidelity of certain PICU Liberation bundle elements is present, or concerns regarding fidelity are identified, modifications to the bundle elements will be considered to maintain the bundle integrity and primary objective of the PICU Liberation program, i.e., improve patient outcomes.Compare PICU-related complication rate between from pre- (before period) and post-implementation (intermediate and after periods, refer to Fig. 3).Conduct focus groups to ascertain learnings from the implementation process and gather feedback from PICU staff about successes and areas for improvement to inform further adaptation, if required.

**Table 4 Tab4:** Definitions of PICU Liberation program: Bundle Performance and Daily Goals (adapted from PUN et al.) [16]

Element	Days eligible	Performance in the last 24 h it was documented that the patient received	Performance in the last 24 h it was documented on the daily goal checklist
A	All days	≥ 6 pain assessments using the FLACC assessments [26, 27]	FLACC goal
B1	Only days when patient received continuous or intermittent sedation	A spontaneous awakening trial (SAT) if receiving continuous or intermittent sedative infusions OR sedation target set as “light” in the daily goals	Suitability for SAT if receiving continuous or intermittent sedative infusions OR suitability for sedation goal set as “light”
B2	Only days when patient was on ventilatory support	A spontaneous breathing trial (SBT) if receiving invasive ventilation	Suitability for SBT if receiving invasive ventilation
B3	Only days when patient was on ventilatory support	An extubation assessments if receiving invasive ventilation	Suitability for extubation assessments if receiving invasive ventilation
C	All days	≥ 6 agitation-sedation assessments using the RASS (Richmond Agitation-Sedation Scale [29]	RASS goal
D	All days	≥ 1 delirium assessments using the CAP-D [31]	CAP-D requested

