**Fig. 4 Fig4:**
[figure not shown]
PICUstars bundle element outcome measures

Control Charts [33] will be used in repeated measure studies for bundle compliance and performance over time since they are an efficient way of measuring practise change in real-time. In reaction to positive or negative change, education and implementation tactics can be tailored. The control chart rules will be used to specify improvement [33, 34].

Before and after implementation, the process of care outcomes will be assessed. Background variables that may act as confounders in the process outcomes will be monitored (e.g., acuity, staffing ratios). The effects of each element and their combinations will provide preliminary estimations of the PICU Liberation bundle’s clinical significance. Absolute and relative risks, followed by logistic regression algorithms to adjust for relevant prognostic risk factors for dichotomous outcomes, will be calculated to assess secondary efficacy outcomes before and after deployment of the bundle. The incremental cost of PICU-related problems, as well as incremental cost effectiveness ratios and 95% confidence intervals, will be estimated for the economic analysis plan [35].

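### Phase 1 versus Phase 4 in one non-randomised PICU is not a factorial matrix, so the promised element and combination effects are not identified by the stated design

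*Protocol article*

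**What the plan says.** The section *Impact measures of the PICU liberation program implementation* adopts Orchestrated Testing, and one of its purposes is to "identify essential components for best practise". It then reasons that "the number of bundle components in Phase 1 represents existing practise and Phase 4 represents bundle implementation, hence a Factorial (or Fractionated factorial) matrix"; it calls such a matrix critical. Later in the same section, after Fig. 4, it adds: "The effects of each element and their combinations will provide preliminary estimations" of the bundle's clinical significance.

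The design is described elsewhere:

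- *Study protocol* calls the study a "single centre prospective before-after hybrid trial-and-implementation quality improvement initiative".
- *Strengths and weaknesses* says that the intervention is "not amendable to blinding of patients, family or clinicians or randomisation".
- *Phase 3* introduces nurse-led check-ins "to ensure communication and application of all relevant bundle elements as clinically appropriate".

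Delivery is recorded in detail. Table 4, "Definitions of PICU Liberation program: Bundle Performance and Daily Goals", sets out for each element which days count and what counts as delivered. Element B1, for example, counts "Only days when patient received continuous or intermittent sedation". Table 2 defines a daily bundle dose, the share of eligible elements that a child received. *Sample size* expects 1800 patients, with delivery that may be complete or partial. The plan and structure for Orchestrated Testing are referred to Fig. 1 and Appendix 1, neither of which is in the text at hand.

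**The concern.** A factorial or fractional factorial analysis separates components because they are set on and off in different planned combinations. The sentence on Phase 1 and Phase 4 describes something else: one unit, its usual practice, and then the bundle. The word linking the two halves of that sentence presents the factorial structure as a consequence of the phases, and it is not one. This is an error in what the article states, not a detail left to an analysis plan.

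At stake is how component results will be read. The article plans a toolkit telling other children's hospitals how to adjust the bundle's features, and its Discussion expects the findings to guide use in other PICUs. A list of essential components presented as the output of a factorial matrix would be taken as causal evidence about each element. On the stated design, an element could look effective because it was delivered more often to children who were already recovering, or because it improved while something else in the unit was changing.

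**Working it through.** The plan attaches no power, error rate or effect size to this analysis, so there is no stated figure to reproduce. The check is one of identification: how many distinct design points the stated contrast supplies, and how many the promised effects need.

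**Inputs**

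- Number of elements, k, from Table 4: 8 letters (A to H); 10 rows if B is split into B1, B2 and B3; 11 if Baby Liberation, which applies to infants only, is added.
- Design points in the stated contrast: 2 (Phase 1, Phase 4).
- Sample: 1800 (*Sample size*).

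**Step 1: what a factorial needs**

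- Main effects: 1 + k parameters.
- Main effects and all two-way terms: 1 + k + k(k − 1)/2.
- Full factorial: 2^k cells.

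With the numbers put in:

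- For k = 8, main effects need 9 parameters; one intercept, 8 main effects and 28 two-way terms make 37; the full factorial has 256 cells.
- For k = 10, main effects need 11 parameters; one intercept, 10 main effects and 45 two-way terms make 56; the full factorial has 1024 cells.
- For k = 11, main effects need 12 parameters; one intercept, 11 main effects and 55 two-way terms make 67; the full factorial has 2048 cells.

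**Step 2: what Phase 1 versus Phase 4 supplies**

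Let p_j be the delivery rate of element j in a phase, β_j its effect, and γ the effect of everything else that changes over calendar time. At phase level, and leaving interactions aside, the difference in mean outcome is

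D = γ + Σ β_j (p_j in Phase 4 − p_j in Phase 1).

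That is one equation in k + 1 unknowns: 9, 11 or 12 for k = 8, 10 or 11. As a matrix check, rows with all elements off and all elements on have rank 2 for each k. Those rows are an illustration, because Phase 1 is existing practice and not zero delivery. The conclusion does not depend on them: any two rows have rank at most 2, whatever the delivery rates. What is identified is a baseline level and one joint bundle-plus-time difference.

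**Step 3: add the intermediate period**

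A third period-level row leaves the rank at 2 if all elements move in step, and raises it to 3 at most if they do not. That is still short of 9.

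**Step 4: use patient-level delivery instead**

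Suppose that element delivery varies independently between 1800 records, at assumed rates of 40% before and 75% after (illustrative; the article gives no such rates). A model with an intercept, a period term, main effects and two-way terms then has 38, 57 or 68 columns, and its rank equals that number in each case. Coefficients can therefore be computed, but they rest on who happened to receive what.

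**Step 5: how thin the combinations are**

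The average number of instances per full-factorial cell is 1800 divided by the number of cells: about 7.0 with 256 cells, about 1.8 with 1024 cells, and about 0.9 with 2048 cells. Patient-days would be more numerous, but days within a child are not independent.

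**Step 6: where confounding enters, from Table 4**

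- B1 depends on sedation, and B2 and B3 on ventilatory support.
- E leaves out days in the lowest mobility class.
- F depends on family presence, which is not a measure of illness.
- Baby Liberation depends on age.
- A, C, D, G and H are eligible on all days. For these, eligibility creates no variation, although actual delivery may still follow severity or workload.

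**The case against.** The strongest reply is that the article does collect element-level information. Delivery is recorded per element and per patient-day, partial delivery is expected, implementation months are described separately, and improvement cycles run for each element. The element effects are called preliminary, possible confounders such as acuity and staffing are to be monitored, and a repeat at another PICU is proposed. Fig. 1 and Appendix 1 might also show more structure.

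Much of this stands, and it rules out some stronger readings that a reader might infer:

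- *That element effects cannot be estimated at any sample size.* Step 4 shows that they can be computed from patient-level variation. The difficulty is what such estimates mean.
- *That Table 4 makes all remaining variation a matter of illness.* Five of the eight lettered elements are eligible every day.
- *That the matrix is known to be all-off against all-on, or that all elements started together.* The article does not set the matrix out. Staggered starts are neither stated nor excluded.

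The reply does not rescue the stated inference. The pointer to Fig. 1 and Appendix 1 concerns the implementation plan; the matrix sentence gives its own rationale, and that rationale is faulty whatever the appendix contains. No schedule of elements by improvement cycle appears in the text. The adjusted regression in the section compares outcomes before and after the bundle and does not use element exposure. Calling the effects preliminary suggests imprecision, not lack of identification, and the aim of finding essential components carries no such caution. The other PICU belongs to a separate proposed study and adds no design points here.

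**Conclusion.** The point holds in this form: the Phase 1 versus Phase 4 contrast supplies 2 design points, against at least 9 needed for main effects of the eight lettered elements and 37 with two-way terms. It identifies one whole-bundle effect, which cannot be separated from calendar time. The promised element and combination effects are not identified by that design. They could only be observational associations from recorded delivery, confounded to an unknown degree and sparse for combinations.

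This rests on three things: one PICU without randomisation, as stated; no planned on/off combinations in the text shown; and the matrix sentence meaning what it says. If the appendix gives separate start dates for elements, some could be separated as steps in time, still without randomisation. The before-after comparison of the whole bundle does not depend on the matrix sentence. The change is worth making because it alters what the study can claim about components.

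**What to change.** In the section on impact measures:

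1. Remove the statement that Phase 1 versus Phase 4 gives a factorial or fractional factorial matrix.
2. State that the before-after comparison estimates the effect of the whole bundle only.
3. Label element and combination results, including any list of essential components, as exploratory associations, adjusted for element eligibility, severity and calendar time. State that they cover only the patient-days on which performance is measured; Table 3 limits these to full 24-hour days from day 3 of the stay.
4. If elements went live on different dates, give the dates and enter them as separate steps in the time series. This would need the twelve baseline months kept separate and not collated into one block.

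A single exploratory model of daily bundle dose against the next day's outcome is a possible addition. It would be a new analysis and is not needed for the correction.

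The cost is a few rewritten sentences, a little extra work for the adjusted element analysis, and the loss of the promise of design-based component effects. No data collection or care changes.

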**Fig. 4 Fig4:**
[figure not shown]
PICUstars bundle element outcome measures

Control Charts [33] will be used in repeated measure studies for bundle compliance and performance over time since they are an efficient way of measuring practise change in real-time. In reaction to positive or negative change, education and implementation tactics can be tailored. The control chart rules will be used to specify improvement [33, 34].

Before and after implementation, the process of care outcomes will be assessed. Background variables that may act as confounders in the process outcomes will be monitored (e.g., acuity, staffing ratios). The effects of each element and their combinations will provide preliminary estimations of the PICU Liberation bundle’s clinical significance. Absolute and relative risks, followed by logistic regression algorithms to adjust for relevant prognostic risk factors for dichotomous outcomes, will be calculated to assess secondary efficacy outcomes before and after deployment of the bundle. The incremental cost of PICU-related problems, as well as incremental cost effectiveness ratios and 95% confidence intervals, will be estimated for the economic analysis plan [35].

### Ethics and dissemination

#### Data management and oversight

The study investigators will be in charge of overseeing the project’s day-to-day operations and ensuring that the ICH-GCP criteria are followed. The data will be monitored by members of the PICUstars research team. Protocol adherence, effective study management, and timely completion of research procedures will all be monitored. On-going surveillance and adherence to the study protocol (intervention fidelity) will be monitored by the principal Investigator (PI) and clinical research nurse (CRN) during monthly audits.

Streamlined data collection instruments and procedures will be used. All other data will be collected by the CRN onto the case report form (CRF) directly from the source data. Data will be entered into a custom-build electronic database developed using the electronic data platform REDCap, hosted by Griffith University [36, 37].

#### Data storage and security

Identifiable data will be stored on institutional network drives, which will be protected by firewalls and other security measures. Hard copies of records will be kept in a locked cabinet in a safe place.

#### Only study personnel will have access to records and data. The data from the study will be de-identified, and a master linking log containing identifiers will be preserved and stored separately from the data. Dissemination

Results will be made available to the funders, critical care survivors and their caregivers, the relevant societies, and other researchers.

## Discussion

The protocol for a single-centre prospective implementation of evaluating the PICU Liberation programme, which adapts the A2F bundle in adult ICU to the PICU of a major children’s hospital in Queensland, is presented in this publication. The goal of the study is to determine the feasibility of adaptation, as well as to evaluate the PICU Liberation trial’s implementation success by assessing the capacity to meet A2F bundle objectives, improve patient quality of care, and optimise children’s recovery while reducing PICU length of stay. Up to 66% of critically ill children can develop PICU-related problems [11]. They not only have a short-term influence on hospital length of stay and cost of care, but they can also cause morbidity, which has long-term detrimental consequences for the child’s quality of life, such as psychiatric, behavioural, and neurocognitive issues (long-term impacts) [11]. There are no paediatric-specific bundles available to aid in the detection and prevention of PICU-related problems [38]. More studies that change from a mortality focus to a quality of survivorship focus are critical [3, 11, 39, 40].

The PICU Liberation project focuses on improving care quality through interdisciplinary team collaboration and best practises for long-term quality initiative implementation. In the adult ICU, there is substantial clinical evidence that the ICU Liberation programme improves patient outcomes significantly and dose-dependently [38].

For a successful implementation, there are necessary conditions: an evidence-based implementation framework, a context appropriate implementation framework, an implementation team leader or facilitator, inter-professional team engagement (nursing, allied health, medical, family), and the ability to customise PICU Liberation to the site needs. This project is designed with these conditions primed. First, it is guided by the Consolidated Framework for Implementation Research (CFIR), which has been shown to facilitate successful bundle adoption and improve the quality of care in adult and paediatric ICUs [25–27, 41]. It will also be guided by the quadruple aim: patient outcomes (including children and family satisfaction), staff satisfaction and work-related wellbeing, cost effectiveness in care, and population health) [28]. Second, several publications go into great detail about the Liberation package, and its implementation has been closely observed by one of our team members overseas, as our content expert and implementation team leader/advisory role. Third, certain aspects of the bundle are ‘adaptable,’ meaning they can be changed to fit a specific situation without jeopardising the intervention’s integrity. We have developed several working groups to adapt and review each of the Liberation bundle elements to ensure feasibility and optimal compliance. Lastly, we have foreseen the main causal factors that influence implementation outcomes (at structural-, organizational-, patient-, provider-, and innovation-levels).

This study is unique in that it includes all aspects of a multifaceted nurse-led PICU model of care in a large cohort of critically ill children, as well as measurement of important clinical outcomes aimed at shifting ICU culture away from the harmful inertia of sedation and restraints and towards an animated PICU filled with patients who are awake, cognitively engaged, and mobile, as well as family members engaged as partners with the PICU team at the bedside. Its advantages include its applicability, clinical team focus, and use of currently accessible resources. PICU Liberation study constitutes a clinical innovation. It was created by the interdisciplinary team and written concisely for intuitive adaptation. The study facilitators will ensure consistency and feasibility of goal setting and Liberation interventions as well as tracking children/s’ and families’ progress. It is designed to be a low tech, high yield clinical and rehabilitation intervention bundle that optimises care through a community of practice and team collaboration, that can be applied to every critically ill child, every day.

The findings of this study will add to our understanding of how to effectively implement optimal care for critically ill children. The research findings will be externally valid and should drive clinical application of the bundle in any PICU because this knowledge will be generalisable to the broader PICU population. Project outcomes and learnings will add to the general body of knowledge about implementation science in the PICU.

The Liberation algorithms allow nurses to readily contribute to goal setting on rounds and provides structure for the nurses to “liberate” their patient. While we believe that the Liberation bundle makes effective use of current resources, we recognise that transferring resources to Liberation interventions may have opportunity costs in certain scenarios. Owing to the nature of this trial-and-implementation health service research, there are notable limitations. The primary limitation of this study is the single-centre design. Given our institution’s standing as the state-wide referral centre, external validity will be achieved by designing the implementation pathway for adaptability in other PICUs locally and nationally.

Second, the PICU Liberation program is not amendable to randomisation or blinding of patients, family, or clinicians. The achieved Liberation assessments and interventions will be recorded by the bedside nurse who is unblinded and part of the intervention. The PICU Liberation facilitator will record achieved Liberation interventions during regular afternoon Liberation check-ins.

Third, to achieve the daily Liberation targets, we do not add additional people resources. This is a setting where current mobilisation, sedation, and ventilation goals are occasionally difficult to achieve. The Liberation bundle, we feel, is complementary to nursing philosophy and will be seamlessly integrated into their system with minimal, if not positive, impact on their workload. It is acknowledged, however, that this budget-neutral approach may not enable effective operationalisation of PICU Liberation, and a dedicated Liberation clinical team may be necessary.

Lastly, successful bundle adoption will create a culture shift from immobilised, sedated patients with limited family presence to comfortable awake patients who are cognitively engaged, and mobile with family members. This highlights a further limitation as bedside nurses become more comfortable applying those principles to all their patients over time, effect size may vary and increase over time, which may lead to a type II error. The high sample size and long post implementation measurement phase of 12 months may help to minimise this.

